# Effectiveness of an interactive telerehabilitation system with home-based exercise training in patients after total hip or knee replacement: study protocol for a multicenter, superiority, no-blinded randomized controlled trial

**DOI:** 10.1186/s13063-017-2173-3

**Published:** 2017-09-21

**Keywords:** Telerehabilitation, Home-based, Total hip replacement, Total knee replacement, Exercise therapy, Aftercare

## Abstract

**Background:**

Total hip or knee replacement is one of the most frequently performed surgical procedures. Physical rehabilitation following total hip or knee replacement is an essential part of the therapy to improve functional outcomes and quality of life. After discharge from inpatient rehabilitation, a subsequent postoperative exercise therapy is needed to maintain functional mobility. Telerehabilitation may be a potential innovative treatment approach. We aim to investigate the superiority of an interactive telerehabilitation intervention for patients after total hip or knee replacement, in comparison to usual care, regarding physical performance, functional mobility, quality of life and pain.

**Methods/design:**

This is an open, randomized controlled, multicenter superiority study with two prospective arms. One hundred and ten eligible and consenting participants with total knee or hip replacement will be recruited at admission to subsequent inpatient rehabilitation. After comprehensive, 3-week, inpatient rehabilitation, the intervention group performs a 3-month, interactive, home-based exercise training with a telerehabilitation system. For this purpose, the physiotherapist creates an individual training plan out of 38 different strength and balance exercises which were implemented in the system. Data about the quality and frequency of training are transmitted to the physiotherapist for further adjustment. Communication between patient and physiotherapist is possible with the system. The control group receives voluntary, usual aftercare programs. Baseline assessments are investigated after discharge from rehabilitation; final assessments 3 months later. The primary outcome is the difference in improvement between intervention and control group in 6-minute walk distance after 3 months. Secondary outcomes include differences in the Timed Up and Go Test, the Five-Times-Sit-to-Stand Test, the Stair Ascend Test, the Short-Form 36, the Western Ontario and McMaster Universities Osteoarthritis Index, the International Physical Activity Questionnaire, and postural control as well as gait and kinematic parameters of the lower limbs. Baseline-adjusted analysis of covariance models will be used to test for group differences in the primary and secondary endpoints.

**Discussion:**

We expect the intervention group to benefit from the interactive, home-based exercise training in many respects represented by the study endpoints. If successful, this approach could be used to enhance the access to aftercare programs, especially in structurally weak areas.

**Trial registration:**

German Clinical Trials Register (DRKS), ID: DRKS00010009. Registered on 11 May 2016.

**Electronic supplementary material:**

The online version of this article (doi:10.1186/s13063-017-2173-3) contains supplementary material, which is available to authorized users.

## Background

In many industrialized countries, the number of hip and knee replacements is rising [1]. According to Organization for Economic Co-operation and Development (OECD) reports, 283 hip replacements and 190 knee replacements per 100,000 population were performed in Germany in 2013, which places Germany second and fourth worldwide, respectively [2]. Furthermore, due to an aging population and increasing obesity rates, a growing number of joint replacements can be expected [1].

After surgery, rehabilitation is an essential part of the therapeutic strategy and can improve function as well as activities of daily living and reduce pain [3]. In Germany, an orthopedic rehabilitation usually lasts 3 to 4 weeks and consists of multidisciplinary therapy elements [4].

The effectiveness of a subsequent rehabilitation for patients after hip or knee replacement is well proven [5–9], but its medium- and long-term sustainability to maintain the therapeutic success remains a major challenge. For this purpose, a subsequent exercise therapy after discharge from rehabilitation is needed [5, 10, 11], but recent data suggest [12] that only half of patients continue with recommended aftercare treatment options after the inpatient rehabilitation. Reasons for this could be the lack of reconciliation with job demands as well as long journeys to treatment-offering facilities. To improve sustainability of postoperative exercise therapy, there is a need for more flexible and individualized treatment options [12].

Telerehabilitation could have the potential to increase the access to therapy in structurally weak areas, where appropriate healthcare structures and offers are missing. Furthermore, telerehabilitation can be performed at any self-determined time and, therefore, could enhance the adherence and compliance, especially of employed patients.

There is an increasing evidence that orthopedic telerehabilitation has positive effects on various clinical conditions. First, investigations demonstrated non-inferiority for telerehabilitation interventions after knee replacement compared to face-to-face interventions [13–17]. However, the investigated telerehabilitation systems mainly differ in terms of implemented features. On the other hand, only insufficient data are currently available for the effectiveness of telerehabilitation for patients after hip replacement [18, 19]. Hence, the effectiveness of telerehabilitation systems needs to be investigated on each system itself. To our knowledge, no study in the German health system investigating the use of a telerehabilitation system in patients after total hip or knee replacement has been evaluated so far.

Therefore, the aim of this study is to investigate the effectiveness of an interactive telerehabilitation system with home-based exercise training considering the function of patients after total hip or knee replacement to ensure or increase the medium- and long-term sustainability of the inpatient rehabilitation success.

## Methods/design

### Study design

In this multicenter, no-blinded, parallel-group randomized controlled trial, patients after hip or knee replacement with a subsequent orthopedic rehabilitation are enrolled in the three participating inpatient rehabilitation centers in Germany. In this study, blinding was not possible due to the nature of the intervention. Assessments are carried out by research associates of University Outpatient Clinic of the University of Potsdam (study site), who are also responsible for giving out the telerehabilitation system to the patients of the intervention group.

The patients are either randomized into the intervention or the control group, using a block randomization with a ratio of 1:1, stratified by the inpatient rehabilitation center. The random code was prepared by the statistical institute in advance and is centrally managed by the study site. The patients are investigated and assessed at the study site within 7 days after their inpatient rehabilitation (Fig. 1).

**Fig. 1 Fig1:**
[figure not shown]
Study design

Patients are eligible for inclusion if a total hip or knee replacement after idiopathic, posttraumatic or congenital osteoarthritis was implanted, they are aged between 18 and 65 years and insured by the German Pension Insurance. Patients without expected functional safety in walking with full load at the end of the rehabilitation are excluded. For those patients, it is assumed that they are not able to perform exercises with adequate load and assessments at the study site. Insufficient skills of the German language in speech and writing also lead to exclusion. For the use of the telerehabilitation system at home, some additional criteria (e.g., High Definition Multimedia Interface (HDMI)-compatible screen, minimum 2.5 m space in front of the screen and Internet access) are required.

The study is conducted in accordance with the principles stated in the Declaration of Helsinki and Good Clinical Practice (International Conference of Harmonization). The study protocol was approved by the Ethics Committee of the University of Potsdam (No. 15/2016) and registered at the German Clinical Trials Register (DRKS00010009). The Standard Protocol Items: Recommendations for Interventional Trials (SPIRIT) checklist is available as an additional file (Additional file 1).

Data protection rules are closely observed and patient data are processed anonymously. All data are documented in paper and pencil form. Before the study, all assessments were determined in a standard operating procedure document including step-by-step instructions to promote data quality. For this purpose, every member of the staff was trained in advance. All data are entered electronically by a research assistant at the study site. The data entry file resembles the data collection paper form and contains programmed plausibility checks including referential data rules, valid value checks as well as range checks. Several research associates control the data independently.

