### Statistics and power calculation

Data will be evaluated descriptively (mean, standard deviation, 95% confidence interval and median for metric variables, frequency and percentiles for categorical variables) for all variables as available case analysis. Inferential statistics will be performed using an intention-to-treat approach including all randomized patients and with multiply imputed data sets for evaluation of the effectiveness of the intervention, as well as a per-protocol approach in patients with complete data sets and without protocol violations for evaluation of the efficacy of the intervention. Baseline-adjusted analysis of covariance (ANCOVA) models (intention-to-treat) will be used to test the primary endpoint for group differences at a level of 5% (two-sided). All continuous secondary endpoints will be analog-tested without adjustment for multiplicity. The rates of return to work status will be compared with the Likelihood-Ratio-Chi^2^-Test. Model assumptions will be checked by testing site × group interactions as extensions of the analysis of covariance (ANCOVA) models.

According to Boardman et al. [30], an improvement of 65–70 m in 6MWD is to be expected by knee or hip replacement followed by standard orthopedic rehabilitation. The study was powered to be able to demonstrate a further improvement of 65 m by telerehabilitation as compared to an improvement of not more than 13 m (20%) in the control group. Assuming an intraclass correlation of 0.3 for the primary outcome and a standard deviation of 84 m [30, 33], 42 patients per group will be needed to reach a power of 80% for the primary analysis. Presuming a 20–25% loss to follow-up, 55 patients per group need to be included in the study to reach the same power in the per-protocol analysis, resulting in a recruitment and randomization of 110 patients in total.

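### Joint type (hip or knee) is neither a stratification factor nor a named ANCOVA term; this costs a little precision, causes no bias, and is cheaply fixed by pre-specifying it as a covariate

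*Protocol article*

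**What the plan says.** All references are to the protocol article.

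- **Population** (Methods/design, Study design, eligibility text after Fig. 1): "Patients are eligible for inclusion if a total hip or knee replacement after idiopathic, posttraumatic or congenital osteoarthritis was implanted". No quota or expected split by joint is given.
- **Allocation** (Study design): patients are allocated "using a block randomization with a ratio of 1:1, stratified by the inpatient rehabilitation center". Center is the only stratification factor.
- **Primary analysis** (Statistics and power calculation): "Baseline-adjusted analysis of covariance (ANCOVA) models (intention-to-treat) will be used to test the primary endpoint for group differences". It is run on multiply imputed data for all randomised patients. Continuous secondary endpoints are tested in the same way.
- **Named model extension** (same section): "Model assumptions will be checked by testing site × group interactions as extensions of the analysis of covariance (ANCOVA) models". No joint × group term is named.
- **Motivation** (Background): non-inferiority has been reported after knee replacement, whereas "only insufficient data are currently available for the effectiveness of telerehabilitation for patients after hip replacement". The aim stated at the end of the Background is nevertheless for hip and knee patients together.
- **Sample size** (Statistics and power calculation): "a further improvement of 65 m by telerehabilitation as compared to an improvement of not more than 13 m (20%) in the control group", with "Assuming an intraclass correlation of 0.3 for the primary outcome and a standard deviation of 84 m". This leads to 42 per group, raised to 55 per group for loss to follow-up.

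**The concern.** Joint type is known for every patient before randomisation and may plausibly be prognostic. If hip and knee patients differ in 3-month walk distance even at the same baseline value, a model without joint type leaves that difference in the error term. Because allocation is not balanced on joint, the hip share can also differ between arms by chance and move the estimate in an individual trial.

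The matter is more tangible for some secondary endpoints. The gait analysis lists hip and knee joint angles for all patients. The hip is the operated joint in some of them and not in others, so pooled angle data mix two kinds of measurement. This needs no assumed figure.

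Pre-specification matters because the trial is open and its assessors are unblinded. A joint covariate or a by-joint table introduced after the data are seen would be open to the charge of having been chosen for its result.

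**Working it through.** **Inputs from the article:** difference 65 − 13 = 52 m; SD 84 m; two-sided 5%; power 80%; 42 per group, 55 after inflation.

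**Assumed, because the article does not give them:** hip share p of 30–70% (50% central); residual hip–knee gap g of 10–40 m in 3-month 6-minute walk distance after baseline adjustment. Since p(1 − p) is symmetric, p = 0.3 also covers p = 0.7 in steps 2 and 3.

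**1. The plan's own figure.** A two-sample t calculation with difference 52 and SD 84 gives n = 41.95, so 42 per group, with power 80.1% at 42. The stated number is reproduced using 84 m as it stands, so 84 m is taken below as the total residual SD.

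**2. Variance explained by joint type.** Share = p(1 − p)g² / 84², where 84² = 7056. At p = 0.5 and g = 40, this is 0.25 × 1600 / 7056 = 5.7%. At p = 0.3 and g = 10, it is 0.21 × 100 / 7056 = 0.3%. The SD after adjustment is sqrt(7056 − p(1 − p)g²).

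| Assumed gap g | Variance share (p = 0.3 to 0.5) | n per group after adjustment | Power at 42 per group |
|---|---|---|---|
| 10 m | 0.3–0.4% | 42 | 80.2% |
| 20 m | 1.2–1.4% | 42 | 80.5–80.6% |
| 30 m | 2.7–3.2% | 41 | 81.1–81.3% |
| 40 m | 4.8–5.7% | 40 | 81.9–82.3% |

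If 84 m were instead the SD within each joint, leaving joint type out would lower power from 80.1% to 77.9% in the worst case (40 m gap, half hips).

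**3. Chance imbalance** (simple-randomisation approximation). The SD of the between-arm difference in hip share is sqrt(2p(1 − p)/n).

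- At p = 0.5 this is sqrt(0.5/55) = 0.095 with 55 per group and sqrt(0.5/42) = 0.109 with 42. A difference of 10 points or more has probability 29% and 36% respectively.
- A difference of 20 points or more has probability 2–4% at 55 per group and 5–7% at 42 (p = 0.3 to 0.5).
- A 10-point imbalance shifts the estimate by 0.10 × g, which is 2–4 m for g = 20–40 m. The standard error is 84 × sqrt(2/55) = 16 m, so the shift is about one eighth to one quarter of a standard error.
- At the 95% limits of imbalance (±17 to ±21 points), the shift is about 3–4 m for g = 20 m and 7–9 m for g = 40 m, against a 52 m target.

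**4. What by-joint results could show.** With half hips there are 21 to 27.5 hip patients per arm (42 or 55 per group).

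- The 95% CI half-width for the hip effect is t × 84 × sqrt(2/n_hip), which is 52 m at 21 per arm and 45 m at 27.5.
- The interaction has SE = 84 × sqrt(2/n_hip + 2/n_knee). A joint × group difference of 52 m then has about 25–37% power across hip shares of 30–70%.

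**The case against.** **Brevity of the article.** It condenses a fuller plan, and further covariates may be listed elsewhere. Calling a model baseline-adjusted does not say that baseline is the only covariate, and surgical data are recorded at the baseline visit. This stands in part. A reader might infer that joint type is controlled nowhere in the trial, and the article cannot establish that. It does fix the stratification factor, and it names a site interaction without naming joint.

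**Chance imbalance is not bias.** This stands in full. A reader might infer that unbalanced joints would distort the result or inflate the error rate. Randomisation covers such imbalance within the 5% level, and adjusting for baseline walk distance removes the part of any joint difference already present at that visit.

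**The gap is assumed.** This also stands. The article's only relevant figure is one expectation of 65–70 m for knee or hip replacement. If the two ends of that range belonged to the two joints, the gap would be 5 m: a 10-point imbalance would shift the estimate by 0.5 m, and the variance share would be 0.25 × 25 / 7056 = 0.09%. That figure describes the gain from surgery plus rehabilitation rather than the later 3-month period, so it does not settle the gap, but nothing in the article documents a large one.

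**No hip hypothesis exists.** A reader might infer from the Background that the trial leaves its own hip question unanswered. The hip evidence gap is motivation, and the stated aim is pooled, so no formal hypothesis goes untested. Nor could this sample answer one reliably, as step 4 of the working shows.

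**Joint angles.** A joint covariate does not resolve the operated versus non-operated side. That is correct: it removes the mean difference between hip and knee patients and no more.

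**Conclusion.** The point holds as a modest weakness in precision. Joint type is absent from the stratification and from the stated model, and it can be added at almost no cost. On the assumed ranges (30–70% hips, 10–40 m residual gap), the gain is 0–2 patients per group, or at most about 2 power points. The planned 42 and 55 per group are not undermined, and the primary test remains valid without the change. The benefit is likely to be clearest for the hip and knee joint-angle endpoints. By-joint effects can only be descriptive. If the full protocol or analysis plan already includes a joint term, the point is met.

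**What to change.** - **Analysis models:** pre-specify joint (hip/knee) as a fixed covariate in the primary ANCOVA and in the ANCOVA models for the continuous secondary endpoints.
- **Imputation:** include joint in the imputation model, so that it matches the analysis model. This matters with 20–25% loss to follow-up expected.
- **Optional reporting:** give the 6-minute walk distance effect with 95% CI by joint, labelled descriptive, with a statement that the trial is too small for a joint-specific conclusion.
- **Randomisation:** leave it as it is. The Trial status section reports 87 of 110 patients included by May 2017, so at most 23 could be allocated under a new scheme.

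The cost is a sentence or two of analysis wording and one degree of freedom per model. No new data are needed, since joint type follows from eligibility. The wording should be fixed before outcome data are examined by arm.

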### Inpatient orthopedic rehabilitation program

All patients undergo a subsequent 3- to 4-week, inpatient, orthopedic rehabilitation program in one of the three participating centers. The program starts within 14 days after surgery. The main components of the multidisciplinary therapy elements are exercise training and physiotherapy, training in activities of daily living, patient education, nutrition and psychological counselling as well as social support to increase patients’ ability to return to work [4]. Patients randomized into the intervention group have two additional 1-h educational sessions with a trained physiotherapist to become familiar with the telerehabilitation system. The latter took part in a structured “train-the-trainer” program in advance which included how to use the system, how to instruct the patients and how to supervise and monitor the intervention. During rehabilitation, potential confounding variables like 6-minute walk distance (6MWD) and range of motion of the joint are documented at admission and at discharge of rehabilitation.

### Intervention

The intervention consists of a 3-month, interactive telerehabilitation with home-based exercise training and is based on the system MyRehab®. It starts within 7 days after discharge from inpatient rehabilitation.

The individually tailored exercise training regarding the choice of exercises (38 different strength and balance exercises) and training modalities (number and sets of repetitions as well as duration of resting time) is created and monitored by the responsible physiotherapist in the rehabilitation center. The patient is instructed to exercise 3 to 4 times a week. The physiotherapist and the patient are always able to communicate via text or voice messages and a video-conference is scheduled on a weekly basis.

The exercises are shown on a screen and the patient is instructed to perform the exercises simultaneously with the system. While exercising, the patient is recorded by a video camera. By tracking the movement pattern, the patient receives an automatic real-time motion feedback in the form of green and red coloration of the single body segments for correct and incorrect movements, respectively. After each exercise, the patient gets a grade evaluating the quality of each exercise as well as the whole training, which can also be seen and interpreted by the physiotherapist in the rehabilitation center for further adjustment of the exercise training.

Patients in the intervention group are allowed to use additional, voluntary, usual aftercare programs, such as exercise-based group training, individualized exercise training or physiotherapy, or to exercise on their own. All performed training options including frequency and duration are recorded in a personal training diary.

### Control condition

Patients randomized into the control group receive voluntary usual care after their inpatient rehabilitation which includes the usual aftercare programs, such as exercise-based group training, individualized exercise training or physiotherapy, or to exercise on their own. Everything is also recorded in a personal training diary. To promote patient retention, especially in the control group, patients are offered an evaluation of their investigations at the study site. Additionally, all patients receive a phone call 1 week before follow-up.

### Assessments

During the baseline visit, sociodemographic (e.g., age, sex, weight, gender, educational level and work ability) and clinical data (e.g., risk factors, comorbidities, pain medication and data of surgery) are documented. Furthermore, the following assessments are performed at baseline and at follow-up 3 months later: functional assessments such as the 6-minute walk test (6MWT) [20] for physical capacity, the Timed Up and Go Test (TUG) [21], the Stair Ascend Test [22], the Five-Times-Sit-to-Stand Test [23] for balance, strength and mobility, the questionnaires Short Form 36 (SF-36) [24] for health-related quality of life, International Physical Activity Questionnaire (IPAQ) [25] for the level of physical activity and the Western Ontario and McMaster Universities Arthritis Index (WOMAC) [26] for pain and stiffness. Measures of function include the assessment of the postural control during double-footed and one-leg stance [27] for left and right leg (barefoot, hands to the hip, view straight forward) for 30 s on a force plate (Amti OR6-6, Advanced Mechanical Technology, Inc. Watertown, MA, USA) as well as gait analysis during over-ground walking (10 trials) with self-selected velocity using a 3D-motion analysis system (12 cameras, Vicon MX; 200 Hz; Vicon Ltd., Oxford, UK) and a kinematic Plug-in Gait lower body model (Vicon Nexus) [28] (see Fig. 2 for the Standard Protocol Items: Recommendations for Interventional Trials (SPIRIT) Figure that the trial follows). Additionally, adverse events (e.g., wound infection, joint luxation) will be documented and evaluated. Further adverse events are not expected due to the constitution of the patients after the inpatient rehabilitation.

